## Aims and hypotheses

### Main Aim: To evaluate the efficacy of the Facebook-based intervention for young adults in a randomized controlled trial

Hypotheses are:Participants receiving the intervention will have higher 7-day point prevalence abstinence at 3-, 6-, and 12-months follow-up compared to those in the control condition.Participants in the intervention condition will demonstrate greater reduction in cigarettes smoked and increased commitment to abstinence at 3-, 6-, and 12-months follow-up than those in the control condition.Participants in the intervention condition will be more likely to make a quit attempt during the 12-month study period compared to those in the control condition.

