### Secondary outcomes

The following secondary outcomes will be assessed at each timepoint:**Reduction of cigarette consumption by 50 % or more (y/n)** between baseline each follow-up will be calculated from the number of cigarettes smoked in the past 7 days at each time point.**Tobacco quit attempt** (y/n). A *Follow-up Smoking Questionnaire* will assess the presence and number of 24 h quit attempts since the last assessment, used to calculate presence of at least one quit attempt in the assessment time period.**Readiness to quit tobacco** will be assessed using the *Stages of Change Questionnaire*, [44] categorizing participants into five stage categories at each timepoint (precontemplation, contemplation, preparation, action, and maintenance), and predictive of quit attempts and cessation [51]. Outcome will be measured as proportion in action or maintenance stage sof change at 3, 6, and 12 month assessments.**Abstinence goal** will be assessed with the *Thoughts About Abstinence Form, *[52]*,* categorizing goal as no goal, intermediary goal (e.g., reduced smoking), or total abstinence. Outcome will be measured as proportion endorsing a goal of abstinence at each timepoint.**Engagement in TSP** will be measured by total number of comments to Facebook study groups during the three-month intervention period.

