### Power calculation

Previous trials of stage-based interventions for smoking cessation [53–57] and trials of Internet interventions for smokers motivated to quit [11, 58] suggest that quit rates for motivated smokers may be as high as 20 % (treatment) and 9 % (control). However, as this will be the first stage-based intervention for young adult smokers delivered over Facebook, and cessation rates in some Internet trials have been as low as 7 % point prevalence abstinence at 3 month follow-up [59], the conservative estimate of 10 % (treatment) and 5 % (control) 7-day point prevalence abstinence at 3, 6, and 12 months follow-up was made. Further, attrition in Internet cessation trials has tended to be as high as 50–75 % at 3 and 6 months follow-up [11, 12, 59]. With 50 % attrition at each time point, and at least one covariate (depending on group differences), a sample size of 480 will provide a minimal power level of .80, and a Type-I error rate of .05 to detect these cessation rates in the most conservative outcome of the study - 7-day point prevalence abstinence.

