### Data analysis

#### Primary analyses

Preliminary analyses will describe and summarize all measures and test the correlation between order of study entry and outcome rates of dropout by condition. If differences for any of these variables are noted, they will be statistically controlled as covariates in model testing. Missing data will be minimized through online assessment. When subjects do not complete online assessments, they will be re-contacted through Facebook or email to obtain missing information. For each hypothesis test, two sets of outcome analyses will be conducted - one with all participants who are maintained in the study, and another based only on biochemically verified smoking abstinence rates to allow for direct comparison of findings with the research literature.

The primary outcome of biochemically-verified 7-day abstinence will be compared between participants in the TSP and Control groups at 3- through 12-months follow up using a mixed-effects statistical model [60, 61]. The independent variables will be intervention versus the control condition, assessment point, plus covariates identified in preliminary analysis. The model will be estimated using maximum likelihood estimation.

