### Secondary analyses

Mixed effects logistic and multinomial regression models for longitudinal ordinal response data to model secondary outcomes for tobacco use and across time (3, 6, 12 months): 1) reduction of cigarettes by 50 % or more (y/n), 2) tobacco quit attempt (y/n; 2 models), 3) action or maintenance stage of change (y/n); and 4) commitment to abstinence (y/n). Independent variables in all models will be treatment condition, abstinence status, and covariates identified as relevant to smoking characteristics in the literature.

To evaluate the secondary aim (effect of a monetary incentive on engagement in the TSP condition), we will test for differences in engagement and primary smoking outcome by incentive groups and the relationship between engagement and primary smoking outcome at 3 months. First, due to expected skewed distribution of the engagement variable (comments), the non-parametric Kruskal-Wallace test will examine overall differences in total number of comments made to the Facebook study group by incentive condition, with test for a linear trend in commenting by incentive frequency. Second, Pearson’s chi-square test will examine 7-day point prevalence abstinence by incentive condition. Abstinence rates will be examined by incentive group. Two sets of analyses will be conducted: one for biochemically verified abstinence, and one for reported abstinence. Finally, Mann–Whitney U tests will compare comments for those abstinent at 3months to those non-abstinent. Again, two sets of analyses will be conducted (one for biochemically-verified abstinence and one for reported abstinence).

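### The term list for the secondary outcome models omits assessment point and condition by assessment point, so as written it gives one averaged effect and not the effects at 3, 6 and 12 months in Hypothesis 2

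*Protocol article*

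**What the plan says.** The Secondary analyses section describes mixed-effects logistic and multinomial regressions to "model secondary outcomes for tobacco use and across time (3, 6, 12 months"). The outcomes are reduction of 50% or more, quit attempt, action or maintenance stage, and commitment to abstinence. The next sentence gives the predictors: "Independent variables in all models will be treatment condition, abstinence status, and covariates identified as relevant to smoking characteristics in the literature".

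The Primary analyses section is more specific about time: "The independent variables will be intervention versus the control condition, assessment point, plus covariates identified in preliminary analysis". Neither model has a condition-by-assessment term.

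Under the Main Aim, the hypothesis on reduction and commitment refers to each follow-up: "Participants in the intervention condition will demonstrate greater reduction in cigarettes smoked and increased commitment to abstinence at 3-, 6-, and 12-months follow-up". The quit-attempt hypothesis does not: "Participants in the intervention condition will be more likely to make a quit attempt during the 12-month study period". The Secondary outcomes section says "The following secondary outcomes will be assessed at each timepoint", and defines quit attempts as those since the last assessment.

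**The concern.** The secondary list is given for all the models, and it leaves out a term that the same Data analysis section names for the primary model. An analyst who follows it fits the three follow-ups together with one coefficient for condition.

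The intervention lasts 90 days and follow-up runs to 12 months, so an effect that is largest at 3 months and fades is a realistic pattern. The Background gives maintenance over one year as a reason for the research. Under fading, a single averaged effect can go wrong in two ways. A real 3-month effect may be diluted below significance, or a significant average may be reported as though it held at 12 months.

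A second problem comes from leaving out assessment point itself. If the outcome becomes more or less common over the visits, and one arm loses more participants at later visits, the arms contribute different mixtures of visits. Part of the time trend then appears as a condition effect.

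**Working it through.** The plan gives no figure to reproduce here. The main check compares the passages, and all rates below are assumed for illustration.

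**1. Terms against hypotheses.**

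| Item | Assessment point | Condition by assessment point | Stated target |
|---|---|---|---|
| Primary model | listed | not listed | 3, 6 and 12 months (Hypothesis 1) |
| Secondary models | not listed | not listed | 3, 6 and 12 months for reduction and commitment (Hypothesis 2); the 12-month period for quit attempt (Hypothesis 3) |

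With condition as the only term involving arm, the model contains one arm contrast. Three visit-specific contrasts need two more parameters.

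**2. What averaging does to a fading effect.** Assumed control rates are 25%, 32% and 40% at the three visits, and intervention rates 45%, 40% and 40%. OR = [p1/(1−p1)] / [p0/(1−p0)].
- 3 months: (0.45/0.55)/(0.25/0.75) = 2.45
- 6 months: (0.40/0.60)/(0.32/0.68) = 1.42
- 12 months: 1.00
- Averaged with equal weights: the rates are (0.45+0.40+0.40)/3 = 0.417 and (0.25+0.32+0.40)/3 = 0.323, so OR = (0.417/0.583)/(0.323/0.677) = 1.49

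These rates were simulated with 120 per arm, latent correlation 0.4 and 300 replicates, using a logistic GEE in place of the mixed model. Condition only gave OR 1.47 (54% rejection). Condition plus visit gave OR 1.47 (53%). Condition by visit gave 2.43, 1.40 and 0.99. So assessment point alone does not recover the visit effects; the interaction does.

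**3. A sharper case.** Assume 35% against 20% at 3 months, 20% in both arms afterwards, and follow-up of 84%, 78% and 72%.
- Averaged intervention rate: (0.84×0.35 + 0.78×0.20 + 0.72×0.20)/2.34 = 0.254
- Averaged OR: (0.254/0.746)/(0.20/0.80) = 1.36
- 3-month OR: (0.35/0.65)/0.25 = 2.15

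Simulations of an effect confined to 3 months (60 to 300 replicates) gave condition-only ORs of 1.33 to 1.40 with 39% to 50% rejection. With 240 per arm, a 3-month two-proportion test rejected in 95%.

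**4. Validity of the average.** In the step 2 simulation with no effect and complete follow-up, the models with and without visit both rejected 5%. With a constant OR of about 2, they gave 1.99 without visit and 2.02 with it, and both rejected 97%.

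**5. Retention that differs by arm, no true effect.** Assumed rates are 25%, 32% and 40% in both arms. Assumed retention is 84%, 78% and 72% in control, and 84%, 67% and 50% in intervention.
- Control: (0.84×0.25 + 0.78×0.32 + 0.72×0.40)/2.34 = 0.3195
- Intervention: (0.84×0.25 + 0.67×0.32 + 0.50×0.40)/2.01 = 0.3106
- Pooled OR: (0.3106/0.6894)/(0.3195/0.6805) = 0.96

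A large-sample GEE on these inputs (20,000 per arm) gave 0.95 without visit and 0.99 with it (standard error of log OR about 0.017). A separate 60-replicate simulation of differing retention gave 0.92 without visit and 1.00 with it. The distortion is modest, and its sign depends on which arm loses more.

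**6. Quit-attempt windows.** Recall since the last assessment covers 3 months, then 6−3 = 3, then 12−6 = 6. The last window is twice as long, so the expected rate differs by visit whatever the arm.

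**7. Abstinence status in the same list.** Assume abstinence of 10% against 5%, all abstinent participants counted as reducers, and 25% reduction among the rest in both arms.
- Total reduction: 0.10+0.90×0.25 = 0.325 against 0.05+0.95×0.25 = 0.2875
- Total OR: (0.325/0.675)/(0.2875/0.7125) = 1.19
- OR among non-abstinent participants: 1.00

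Conditioning on abstinence removes the part of the effect that works through quitting.

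**The case against.** The strongest reply is that the condition term does test a hypothesis: whether the arms differ over follow-up. That is a fair reading of Hypothesis 2, and one averaged test is a defensible choice over three. This stands. A reader might infer that the secondary models cannot test their hypotheses at all, or that the test is invalid. The documents do not support that, and step 4 shows normal behaviour with complete follow-up.

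Second, the primary model has no interaction either, so the comparison with it explains only the missing assessment point. This also stands: a fading effect is averaged in the primary model too.

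Third, quit attempts are hypothesised over the 12-month period and stage of change appears in no hypothesis, so the visit-specific argument covers reduction and commitment only. This is accepted. The unequal recall windows are a reason to include assessment point, not to demand visit-specific quit-attempt tests.

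Fourth, the wording about modelling across time suggests that time was intended, and a condensed article may leave detail to a fuller document. That makes an oversight in wording plausible. It does not remove the point, because the article states the terms for all the models and the stated terms leave time out.

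Finally, the illustrations assume strong fading and use GEE without the listed covariates. They show direction, not the expected size in this trial.

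**Conclusion.** The point holds in a limited form. The stated terms for the secondary models omit assessment point and condition by assessment point. Each model therefore gives one average condition effect and cannot show whether reduction and commitment differ at 3, 6 and 12 months. The average is also open to modest distortion where rates change over visits and retention differs by arm (OR 0.92 to 0.96 in place of 1.00 in the illustrations).

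How much is lost depends on the unknown time course. If the effect is constant, almost nothing is lost as a test of the average. If it is confined to 3 months, an OR of about 2.2 at that visit appears as roughly 1.3 to 1.4 overall. These sizes rest on assumed rates, correlations and retention. The textual conclusion does not depend on them.

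This concerns secondary outcomes and should be corrected, but it does not undermine the trial.

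**What to change.** In Secondary analyses, restate the terms as follows.
- All secondary models: condition, assessment point (3, 6, 12 months as categories), and the stratification factors (stage of change; daily or non-daily smoking). The last are added because randomisation was stratified on them and the protocol describes them as related to outcome.
- Reduction and commitment: add condition by assessment point. Report the condition effect at 3, 6 and 12 months with a joint test over the three, alongside the average effect.
- Quit attempt: no visit-specific test is needed for the hypothesis as worded, but keep assessment point because of the unequal recall windows.
- Abstinence status: say whether it stays. It is measured after randomisation and is what the intervention aims to change, so if it is kept the condition effects are not total treatment effects and should not be described as such.

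The cost is a few lines of analysis text and no new data. The interaction adds two parameters per model, and intervals at single visits will be somewhat wider than for the average.

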## Methods/Design

### Overview of design

This study is a randomized controlled trial (RCT) with 480 young adults age 18 to 25 recruited through Facebook (Fig. 1). Participants are randomized to one of two conditions: (1) the Tobacco Status Project motivationally-tailored smoking cessation intervention delivered through Facebook (TSP); or (2) a control condition (referral to the Smokefree.gov website). Assessments are conducted online at baseline, 3-, 6-, and 12-months follow-up. Primary outcome is biochemically-verified 7-day point prevalence abstinence from tobacco, and secondary outcomes are reduction in cigarettes smoked per week, 24 h quit attempts, and commitment to abstinence in each time period. Within the TSP group, a monetary engagement will be tested as a moderator of engagement and abstinence.

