### Study procedure

Informed consent is obtained from all study participants in accordance with the Helsinki Declaration and approved by the UCSF Committee in Human Research (#11-06294). During the informed consent process, participants’ understanding of the information provided is assessed through a series of multiple choice questions with required responses before being able to proceed with the study. Questions are based on those used in studies with potentially vulnerable populations [41, 42]. Any wrong answers during the consent process are sent to study staff who then contact a potential participant via email or Facebook for further clarification of the consent process. Therefore, no participant will be enrolled that has not answered all consent questions correctly. Participants consenting to participate in the study are asked to verify age by sending proof through email or social media. Verified participants are emailed a baseline assessment. Those completing the baseline assessment are randomized to receive either the Tobacco Status Project (TSP) intervention of referral to the Smokefree.gov website (control).

A stratified random assignment program was developed and participants are assigned from within stratified blocks immediately after completing the baseline assessment. Participants are stratified on stage of change (precontemplation, contemplation, preparation) and smoking pattern (daily vs. non-daily), variables known to be related to outcomes and addressed by the intervention [43]. Participants in the TSP group are assigned to “secret” (private) Facebook groups based on their readiness to quit tobacco. Groups begin when there are approximately 10 participants enrolled, as that has been deemed the optimal number based on analyses of engagement in our previous work [37] ([name], [name], [name]: Smoking cessation intervention on Facebook: Which content generates the best engagement?, submitted). Participants in the control condition are given a referral to the Smokefree.gov program and are encouraged to use it as much as they would like.

Assessments occur online using the survey program Qualtrics at baseline, 3, 6, and 12 months follow-up. Participants receive their choice of gift cards in the amount of $20 per assessment, and a $20 bonus for completing all three assessments, for a total possible stipend of $100 for completing all assessments.

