### Treatment conditions

#### Tobacco Status Project (TSP)

The TSP is a smoking cessation intervention implemented entirely through “secret” (Facebook’s word for entirely private) Facebook groups. All TSP participants are assigned to a Facebook group based on their TTM stage of change (precontemplation: not ready to quit in the next 6 months; contemplation: intending to quit in the next 6 months; or preparation: ready to quit in the next month and demonstrating at least one past year quit attempt).

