**Fig. 2 Fig2:**
[figure not shown]
Tobacco Status Project Sample Posts

Second, the intervention incorporates weekly “The [name] In” live sessions with a PhD level smoking cessation counselor (using FB commenting features), during which a counselor provides some limited content for discussion and participants can ask questions and get supplemental support. Content for sessions is tailored to readiness to quit tobacco and is based on Motivational Interviewing (MI) and cognitive behavioral coping skills for smoking cessation.

Third, six manualized 45-min state-of-the-art smoking cessation counseling sessions based on cognitive behavioral therapy (CBT) were adapted for social media delivery for this study. These sessions are designed to be delivered in Facebook events and events are scheduled in each group separately. In contrast to The [name] In sessions that are conversational and question and answer-based, these sessions present more material, and are designed to help participants who are motivated to quit. Thus, only participants in preparation groups are offered these CBT sessions and participants may opt to participate in the sessions at any time during the 90 days of Facebook intervention. In all groups, links to more intensive treatment in a participant’s’ area are available as needed.

Additionally, we are testing an incentive structure in which the TSP groups are randomized to one of four incentive conditions tied to engagement in the intervention: 1) daily; 2) weekly; 3) monthly; or 4) no incentive. Participants in daily, weekly, or monthly groups can earn money based on comments made to daily Facebook posts at the end of each period. At the end of the 90-day intervention, all participants in paid incentive conditions receive a gift card in the amount they have earned up to $90. This is separate from the $100 participants could earn for completing all study assessments.

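### Incentives are randomised to whole Facebook groups, but the named tests of the incentive effect treat participants as independent, so type I error exceeds 5% by an amount that depends on an unstated within-group correlation

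*Protocol article*

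**What the plan says.** All places are in the protocol article.

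- **Unit allocated.** Under Treatment conditions, Tobacco Status Project (TSP), the incentive paragraph says that "the TSP groups are randomized to one of four incentive conditions tied to engagement in the intervention". The four conditions are daily, weekly, monthly and none.
- **Size of the unit.** Study procedure: "Groups begin when there are approximately 10 participants enrolled".
- **How the unit is formed.** Tobacco Status Project (TSP): "All TSP participants are assigned to a Facebook group based on their TTM stage of change".
- **Engagement outcome.** Secondary outcomes defines it as "total number of comments to Facebook study groups during the three-month intervention period".
- **Tests.** Secondary analyses plans a Kruskal-Wallis "test will examine overall differences in total number of comments made to the Facebook study group by incentive condition", adds a linear trend over incentive frequency, and states that Pearson's "chi-square test will examine 7-day point prevalence abstinence by incentive condition".

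No term for Facebook group or stage appears in these tests. The mixed-effects models under Primary analyses and Secondary analyses serve the smoking outcomes over time. They are not applied to the incentive aim and name no group effect. The stratification by stage and smoking pattern in Study procedure concerns participants allocated to TSP or control. The article does not say whether the assignment of groups to incentives is balanced by stage.

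**The concern.** The incentive comparison is a cluster-randomised comparison nested in the TSP arm. Members of a group share one private thread, see the same daily posts and take part in the same live sessions, which run through commenting. Their comment counts are therefore likely to be correlated. A lively or a silent group moves about ten observations at once. With about six groups per condition, such differences do not average out as they would over 60 independent people.

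Kruskal-Wallis, the trend test and Pearson's chi-square all take their reference distributions from independent observations. With positive within-group correlation they understate the chance variation between conditions. The trial could then report that paying for engagement works, or that one payment schedule is better, when it has only seen ordinary variation between groups. Because the tests are named, this is a stated analysis that does not match the allocation, and not a detail left to an analysis plan.

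**Working it through.** **Plan's own figure.** There is none to reproduce. The article gives no sample size, power or ICC for the incentive comparison. The .80 and .05 under Power calculation concern cessation in TSP versus control and are not used here.

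**Inputs.**
- Total 480 (Overview of design). The split is not stated; 1:1 is assumed, giving 480/2 = 240 in TSP.
- About 10 per group (Study procedure): 240/10 = 24 groups; 24/4 = 6 per condition. Equal sizes are assumed.
- Abstinence 10% and attrition 50% (Power calculation): 10 × 0.5 = 5 observed per group.
- 61% commented at least once in the feasibility trial (Background), so 39% zeros in a check for ties.
- ICC: assumed, 0 to 0.30.

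**Step 1, design effect.** DE = 1 + (m − 1) × ICC. With m = 10:
- ICC 0.02: 1 + 9 × 0.02 = 1.18
- ICC 0.05: 1 + 9 × 0.05 = 1.45
- ICC 0.10: 1 + 9 × 0.10 = 1.90

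At ICC 0.10 the 240 participants carry the information of about 240/1.90 = 126.

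**Step 2, approximate type I error.** A four-group test at 5% rejects when its statistic exceeds 7.815 (chi-square, 3 df). Under clustering the statistic is inflated by about DE, so the true error is about P(χ²₃ > 7.815/DE). This gives 8.5%, 14.5% and 25.0% at ICC 0.02, 0.05 and 0.10.

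**Step 3, simulation with no incentive effect.** 24 groups, 6 per condition, 4,000 runs (simulation standard error at most √(0.25/4000) = 0.8 percentage points). Comments use a normal group effect; the tests depend on ranks only, so skewness does not matter. The article names no trend statistic, so Spearman's was used. Abstinence is beta-binomial at 10%.

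| Assumed ICC | Kruskal-Wallis, comments | Trend, comments | Chi-square, 10 observed per group | Chi-square, 5 observed per group |
|---|---|---|---|---|
| 0 | 5.0% | 5.3% | 4.5% | 4.6% |
| 0.01 | 5.6% | 5.6% | 6.5% | 5.4% |
| 0.02 | 7.8% | 7.0% | 8.0% | 5.6% |
| 0.05 | 13.7% | 10.0% | 13.2% | 7.9% |
| 0.10 | 24.8% | 15.3% | 23.6% | 12.2% |
| 0.20 | 42.8% | 23.8% | 43.3% | 19.7% |

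The Kruskal-Wallis column agrees with Step 2. With 39% zeros (2,000 runs) it becomes 7.9%, 12.4% and 23.4% at ICC 0.02, 0.05 and 0.10, so ties do not remove the problem. The last column is lower because DE falls with five per group: 1 + 4 × 0.10 = 1.40 at ICC 0.10.

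**Step 4, analysis by group.** An analysis of variance of the 24 group means (24 − 4 = 20 error df) on the same simulated comments rejects in 4.4% to 5.2% of runs at every ICC from 0 to 0.30.

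**Step 5, stage alone.** Assume eight groups per stage, no other clustering, and a difference of 0.3, 0.5 or 0.8 SD in commenting between precontemplation and preparation. If groups are allocated without regard to stage, Kruskal-Wallis error is 7.1%, 11.5% and 25.0%. If allocation is balanced by stage, it is 4.5%, 4.0% and 3.2%. Stage is one source of between-group variation, so these figures should not be added to those in Step 3.

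**The case against.** **The size rests on an ICC that the article does not give.** This stands. A reader might infer that the false positive rate is far above 5% in every case. The document does not support that: at ICC 0.01 Kruskal-Wallis gives 5.6%, and for abstinence with half the participants observed the excess is small up to ICC 0.05. The direction does not depend on the value.

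**Kruskal-Wallis might be meant for group totals.** The phrase about comments made to the study group allows this reading. But the same section compares comments between abstinent and non-abstinent people, so the count is held per participant. The chi-square on abstinence is at participant level in any case.

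**Stage imbalance is not established.** This stands. Taking the 13% prepared to quit at feasibility baseline gives 240 × 0.13/10 = 3.1 preparation groups for four conditions, and a reader might infer that one condition must have none. That share comes from 79 participants whom the Discussion describes as limiting generalisability, and the stage mix here is unknown. If assignment was balanced by stage, the planned test is slightly conservative with respect to stage.

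**Two further inferences do not follow.**
- Few expected abstainers (60 × 0.10 = 6 per condition, or 30 × 0.10 = 3 with attrition) might suggest that chi-square fails for that reason too. Without clustering it rejected in 4.6% of runs at five per group, so sparse counts do not cause the false positives.
- The Mann-Whitney test of comments by abstinence might seem to share the error. It does not compare randomised conditions; any confounding there is a separate matter.

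**The aim is secondary.** It has no directional hypothesis and no stated error rate of its own. That lowers the priority but does not make the tests fit the allocation.

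**Conclusion.** The point holds: the incentive is allocated by group and tested by participant. Type I error exceeds the nominal level for any appreciable within-group correlation. The excess is likely to matter most for comments, where shared threads make clustering plausible, and is roughly halved for abstinence if half the participants are lost. Stage imbalance may contribute if the assignment of groups to incentives ignored stage, and does not if it was balanced.

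The figures assume 1:1 allocation, 24 equal groups, six per condition, and the ICCs shown. This should be corrected, at the priority of a secondary aim. A reader might infer that it undermines the TSP-versus-control comparison; nothing in this point bears on that comparison.

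**What to change.** In Secondary analyses, replace the participant-level incentive tests with an analysis by the unit randomised. One suitable form is a permutation test that re-allocates whole groups among the four conditions, within stage if the assignment was stratified by stage. Use group means of ranked or log comments for engagement and group proportions for abstinence, with a trend statistic ordered none, monthly, weekly, daily. A comparison of group-level means is an acceptable alternative. State how groups were assigned to incentives, so that the permutation matches it.

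A logistic mixed model is not a good remedy for abstinence. At 10% there are 240 × 0.10 = 24 abstainers, or 12 with 50% attrition. Three incentive terms and two stage terms would leave about 24/5 = 4.8 or 12/5 = 2.4 events per fixed parameter, before the group effect.

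The cost is a change of analysis wording and wider intervals, because there are about 24 units and not 240. No new data are needed beyond each participant's group.
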